## 1. Background and Rationale

Point-of-care ultrasound (POCUS) has matured to an essential diagnostic tool [1], particularly in perioperative, emergency and intensive care settings [2–4]. However, teaching of ultrasonography in medical school still remains limited and teaching approaches are highly variable [5,6]. Integration of structured trainings for ultrasonography in medical curricula is thus highly needed.

POCUS is quick, non-invasive, and performed at the bedside which is particularly helpful for the assessment of critically ill patients [7,8]. Several algorithms were developed to standardize ultrasound examinations and to create a common language to communicate diagnostic signs. The probably best-established algorithm is Focused Assessment with Sonography for Trauma (FAST) [9]. However, while FAST is easy to perform, it lacks the ability to diagnose several non-traumatic causes for hemodynamic instability. Rapid Ultrasound for Shock and Hypotension (RUSH) complements the FAST algorithm by several sonographic views to assess almost all clinically relevant causes for hemodynamic instability [10,11], shown to provide a good diagnostic accuracy [12]. However, RUSH is associated with lower teaching success than FAST, most probably due to increased complexity [13]. There is thus further need to assess the learning outcomes of teaching RUSH in medical students.

Ultrasound teaching courses often use young and healthy models for practical trainings. However, real patients are often considerably harder to scan; for example, obesity may impede scanning performance [14]. The evaluation of learning outcomes should thus include the assessment of scanning performance under clinical conditions.

This prospective observational study therefore aims to evaluate the learning outcomes of medical students after participating a single-day training in RUSH with a focus on performance under clinical conditions. We will primarily evaluate the clinical performance by a newly created performance score for RUSH and the time needed to perform the examination. Secondary outcomes will be the participants' knowledge before and after the course, performance in a final objective structured clinical examination (OSCE), and the results of a subjective evaluation by the participants.

## 2. Study Objectives

We propose a prospective observational single-cohort study assessing the learning outcomes of medical student that participate a course for point of care ultrasound for medical emergencies according to the RUSH protocol (Rapid Ultrasound for Shock and Hypotension). The proposed study will have the following aims:

### **Primary Aim 1**

To evaluate clinical scanning performance by a newly created performance score for RUSH over several examination attempts on intensive care or postoperative patients after participating a single-day introductory training course.

Hypothesis. None (descriptive)

### **Primary Aim 2**

To evaluate the time needed to perform RUSH over several examination attempts on intensive care or postoperative patients after participating a single-day introductory training course.

Hypothesis. None (descriptive)

### **Secondary Aim 1**

To evaluate the practical learning success of the participants by an objective structured clinical examination (OSCE).

Hypothesis. None (descriptive)

### **Secondary Aim 2**

To evaluate the theoretical learning success by comparing the theoretical knowledge of the participants before and after course completion.

Hypothesis. We hypothesize that course participation will increase the score achieved in a written exam performed before and after the course.

### **Secondary Aim 3**

To obtain the subjective evaluation by the participants.

Hypothesis. None (descriptive)

### 3. Methods and Study Design

#### A) Study Overview

We propose a prospective single-center observational study to evaluate the clinical performance of medical students and teaching outcomes after a single-day training in ultrasound for medical emergencies according to the RUSH protocol (Rapid Ultrasound for Shock and Hypotension). The participants will receive a prereading for the course providing a detailed description of the RUSH protocol. At the beginning of the course, the participants' knowledge will be assessed by a written entry exam. The first day of training will include theoretical lectures, practical demonstrations, and exercises on the simulator and among the participants. On the second day, we will evaluate the practical performance of the participants in carrying out RUSH on patients in the intensive care unit or in the recovery room. On the third day, the practical performance of the participants will be evaluated by an objective structured clinical examination (OSCE) on an ultrasound simulator and the written entry exam will be repeated to evaluate the participants' gain in theoretical knowledge. Additionally, each participant will have to provide a subjective evaluation of the course.

## B) Course Overview

### **Prereadings (approx. 2 – 4 hours):**

- 1) Bowman, Boitnott and Miesemer (2017). THE Point of Care ULTRASOUND HANDBOOK - The RUSH Exam: FOAMed edition. EMSPOCUS.  
(<https://emcrit.org/wp-content/uploads/2018/03/RUSH-FOAMed-Version-w-Corrections-better.pdf>)
- 2) The Pocus Atlas: [thepocusatlas.com/shock](http://thepocusatlas.com/shock)

### **Day 1 – Training (6 hours):**

- Entry test (20 MC questions)
- Theory: Ultrasound basics; Shock; RUSH protocol; Pathology quiz
- Practical exercises with demonstrations of common pathologies on the simulator
- Practical exercises among the participants

### **Day 2 – Practice under clinical conditions (about 4 hours per group):**

- Short repetition of the theory
- RUSH examinations of intensive care or postoperative patients
- 3 examinations each on a separate patients will be performed

### **Day 3 – Exams:**

- Final practical exam (OSCE)
  - Demonstration of the RUSH protocol on a participant with normal findings
  - Identification of a pathology on the simulator with RUSH
- Repetition of the entry test (20 MC questions)

### C) Study Population

Ethical approval will be obtained prior to study execution. Informed consent and data use agreements will be obtained from each participant of the study.

#### **Inclusion criteria**

- Medical students willing to participate in the course.
- Medical students within the clinical period of study (lower years preferred).

#### **Exclusion criteria**

- Extensive ultrasound experience (e.g., previous participation in equivalent ultrasound courses).
- Final (practical) year medical student.

### D) Exposure

The above-described day 1 of an introductory academic teaching course for RUSH.

## E) Outcomes

### **Primary Outcome 1: *Performance score.***

Each ultrasound examination performed on patients will be scored based on a standardized protocol (performance score). The results will be expressed as the percentage of achieved points of the totally achievable points.

#### ***Scoring of the ultrasound examination performance***

*Each ultrasound view included in the RUSH protocol will be rated as “fully acquired” (2 points), “partially acquired” (1 point), “not acquired” (0 points) or “not possible”. Views that cannot be scanned, e.g. due to dressings, reduce the maximum number of achievable points. Only one examination will be carried out and scored per patient. For more details, please review the enclosed documents “Performance Score” and “Ultrasound View Rating Criteria”.*

### **Primary Outcome 2: *Performance Time.***

The time needed to perform each examination measured accurate to the second.

### **Secondary Outcome 1: *Score in the practical exam (OSCE)***

The performance score (secondary outcome 1) will be extended by an evaluation of the diagnostic and documentation skills of the participants during simulation.

*Additional to the performance score, we will score whether the participant makes the right diagnosis after performing RUSH on a simulator (scoring according to the simulator’s program). Furthermore, the participants must write a medical report. The reports are rated as “good” (2 points), “moderate” (1 point) or “insufficient” (0 points). The overall result will be expressed as percentage of the maximum achievable points. For more details, please review the enclosed document “OSCE Checklist”.*

### **Secondary Outcome 2: *Score in the written exams***

A written exam will be performed before and after the course. The exam will consist of 20 questions (predominantly multiple choice). The results will be expressed as percentage of the maximum achievable points.

### **Secondary Outcome 3: *Subjective evaluation by the participants***

Each participant will get an evaluation sheet with several items to score. The overall rating of the course with a scale of 0 to 10 (0 worse and 10 best scoring) will represent the most important tertiary outcome 3. For further detail, please review the enclosed document “RUSHPRO Evaluation Sheet”.

## F) Data Analysis

Data will be presented as means (SD) or medians (IQR) according to data distribution.  $P < 0.05$  will be considered statistically significant.

### **Primary Outcomes 1 and 2:**

#### ***Performance Score, Performance Time.***

The obtained Performance Scores and Performance Times over the attempts will be summarized with a mean for each participant and graphically displayed.

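### The only numerical summary stated for both primary outcomes is a per-participant mean that drops attempt order, and the accompanying graph is not said to be by attempt

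*Protocol*

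**What the plan says.** Protocol section 2 gives two primary aims. The first is "To evaluate clinical scanning performance by a newly created performance score for RUSH over several examination attempts on intensive care or postoperative patients", and the second is "To evaluate the time needed to perform RUSH over several examination attempts on intensive care or postoperative patients". Both are declared descriptive, with no hypothesis.

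Section 3.B, Day 2, fixes the number of attempts: "3 examinations each on a separate patients will be performed". Under section 3.E each patient examination receives its own performance score, and the time outcome is "The time needed to perform each examination measured accurate to the second". Section 3.D defines the exposure as day 1 of the course only.

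Section 3.F, under Primary Outcomes 1 and 2, states the analysis: "The obtained Performance Scores and Performance Times over the attempts will be summarized with a mean for each participant and graphically displayed". The general rule at the start of section 3.F allows mean (SD) or median (IQR) according to distribution, but does not say that it is applied by attempt. The protocol states no by-attempt summary, change or trend.

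**The concern.** The aims name performance across several attempts, and the data are recorded attempt by attempt. The stated summary reduces the three values to one number per participant and discards their order.

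Order has a meaning in this design. Because the exposure is day 1 alone, attempt 1 on day 2 is the first patient scan after it. Attempts 2 and 3 also follow one and two practice scans on patients. The mean blends performance just after the training with performance after further practice and reports neither separately.

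In a descriptive study the summary is the result. As stated, it could report the same figure for a cohort that improves, stays level or declines over its patient scans. If the by-attempt presentation is not fixed beforehand, the choice of which attempt or average to emphasise could also be made after the data are seen.

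**Working it through.** The protocol gives no sample size, effect size or SD for these outcomes, so there is no planned figure to reproduce. The check concerns what the stated summary retains.

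**Inputs from the protocol**
- Attempts per participant: 3, each on a separate patient (section 3.B, Day 2).
- Unit of measurement: the single examination, for both score and time (section 3.E).
- Stated numerical summary: one mean per participant over the attempts (section 3.F).

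**Step 1: weights.** Let y1, y2, y3 be one participant's values.
- Mean = (y1 + y2 + y3)/3, with weights (1/3, 1/3, 1/3).
- Change from first to third attempt = y3 - y1, with weights (-1, 0, 1).
- Inner product = (1/3)(-1) + (1/3)(0) + (1/3)(1) = 0.

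The two are orthogonal. A linear course around a given level can be made steeper, flatter or reversed without altering the mean.

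**Step 2: illustration.** The scores are assumed, in % of achievable points.

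| Sequence | Mean | Slope per attempt | Attempt 3 minus attempt 1 |
|---|---|---|---|
| 50 / 70 / 90 | 70 | +20 | +40 |
| 70 / 70 / 70 | 70 | 0 | 0 |
| 90 / 70 / 50 | 70 | -20 | -40 |

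The stated summary is 70 in every row. The same algebra applies to time.

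**Step 3: the price of looking by attempt.** Assume equal variance at each attempt and a common correlation r between two attempts by the same participant. Relative to the variance of a single attempt, the mean has variance (1 + 2r)/3 and the change has variance 2(1 - r).

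| r (assumed) | Mean | Attempt 3 minus attempt 1 |
|---|---|---|
| 0 | 0.33 | 2.0 |
| 0.3 | 0.53 | 1.4 |
| 0.5 | 0.67 | 1.0 |
| 0.7 | 0.80 | 0.6 |

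Scan-to-scan noise, such as patient difficulty, with variance s² contributes s²/3 to the mean and 2s² to the change. That is 2 ÷ (1/3) = 6 times as much. The mean is the steadier measure of level, and the change is noisier per participant with respect to patient difficulty.

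**The case against.** **The graph may show the attempts.** The same sentence promises a graphical display, and its wording permits a plot by attempt. In a descriptive study a graph is a legitimate way to present a primary result. This stands. A reader might infer that the plan makes it impossible to see performance across attempts, and the protocol does not support that. What remains is that the graph's content is undefined: the sentence equally allows a plot of the per-participant means.

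**The aims may mean an average.** Evaluating performance "over several examination attempts on intensive care or postoperative patients after participating a single-day introductory training course" can be read as pooling across attempts, and the aims do not mention change, improvement or a learning curve. The mean would answer that reading. This also stands in part. A course over the attempts is the more natural reading, but it is not the only one, so it cannot be said that the stated summary fails the primary question outright.

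**Averaging has a rationale.** Section 1 notes that real patients can be considerably harder to scan, and section 3.E allows for views that cannot be obtained. Each attempt is on a different patient, so averaging three reduces that noise. This stands, and it is the reason to keep the mean.

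**Unequal numbers of attempts.** A reader might also infer that participants with fewer scans would be biased relative to those with three. The protocol plans three for every participant and describes no shorter series, so this is hypothetical and forms no part of the point.

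**Conclusion.** The point holds in a limited form. The one numerical summary stated for both primary outcomes drops attempt order, carries no information on a linear course over the three attempts, and does not separate the first scan after the training day from the later ones. The accompanying graph is not defined. This is a choice written into the protocol, not a detail left for a separate analysis plan.

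Its size cannot be given from the documents. Under the assumed scores above, a 40-point rise and a 40-point fall leave the same mean. How much is hidden in practice depends on how far performance changes over three scans, for which the protocol gives no figure.

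It is not a must-fix. Every examination is scored and timed individually, no hypothesis or sample size rests on this summary, and by-attempt results can be produced from data already planned. The conclusion assumes that the order of the three examinations is recorded with each score and time.

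**What to change.** In section 3.F, Primary Outcomes 1 and 2, replace the sentence with wording such as:

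> Performance Score and Performance Time will be summarised separately for attempts 1, 2 and 3 as mean (SD) or median (IQR) according to distribution. Individual trajectories will be plotted by attempt. The within-participant change from attempt 1 to attempt 3 will be described with a 95% CI. The mean over the three attempts for each participant will be reported as an additional summary of overall level. Because each attempt is on a different patient, by-attempt values and changes will be interpreted descriptively.

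A mixed model with attempt as a three-level factor and a random intercept for participant is an option, but a study declared descriptive does not need it.

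The cost is a few lines of text and simple tabulation, with no new data or participants. The small downside is that by-attempt values and changes include patient-difficulty noise that the average partly smooths out. The last sentence of the proposed wording and the retained mean deal with that.

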### **Secondary Outcomes 1 and 3:**

#### ***Score in the practical exam (OSCE), Subjective evaluation by the participants***

The obtained scores and the results of the subjective evaluation will be described in a table or graphical format.

### **Secondary Outcome 2: Score in the written exams**

The obtained scores before and after course participation will be compared by an unadjusted bivariate statistical test for paired samples according to the obtained distribution (paired t-test or Wilcoxon signed-rank test).

## G) Sample Size Considerations

This is a descriptive study. Thus, no a priori sample size estimation was performed. The highest number of participants possible, regarding available teaching resources, will be included in this study.

## 5. Attachments

- RUSHPRO Performance Score
- RUSHPRO Ultrasound View Rating Criteria
- RUSHPRO OSCE Checklist
- RUSHPRO Evaluation Sheet (pending)
